## 6.2 Randomisation, blinding and treatment allocation

If they sign the informed consent form they will be randomly allocated to one of the two treatment groups (A or B) using the Randomization Tool in Castor. Patients will be randomly assigned to one of the two study groups (A or B). A website randomisation program built within Castor will be used for the randomization. After informed consent, patients will be randomized. This is a single blind study, meaning that only participants are blinded for the treatment allocation. The surgeons cannot be blinded, as they will know which procedure they performed. The surgeon will not write down which procedure the patient received in the surgical report or in the letter to the general practitioner. It will only be recorded in Castor and in the RFS map. De blinding (single-sided) will only be lifted if it is in the interest of the safety of the participant. De participant and/or general practitioner can request this from the treating physician (ENT-surgeon) who performed the surgery. The ENT-surgeon will decide if lifting of the blinding is necessary and inform the researcher about this event. Only in case of medical emergency and in absence of the treating physician, other medical specialists can lift the blinding by checking the placement of the patient in the RFS map. All medical specialists have access to the RFS map with information of the participants where an inclusion table with randomization is stored. This way it is possible to lift blinding 24 hours a day.

Stratification will be used to distribute the two groups as evenly as possible between the participating centres. Patients are randomized into one of two groups in an equal 1:1 allocation ratio. A 4,6,8 block randomization will be used.

### 6.3 Study procedures

The procedures and tests will be administered during the standard care process. The only extra procedures are the informed consent procedure, randomization process and the collection of questionnaires. The baseline characteristics, preoperative CT-scan, operative report, postoperative DW-MRI scan, and pre- and postoperative audiometric measurement will be collected and extracted from the electronic health record. The questionnaires and randomization will be performed and collected in Castor EDC. A clinical research file (CRF) is created to store all data, which is added to the database in Castor EDC (Amsterdam, the Netherlands). A research imaging archive (RIA) will be used to store the medical images which will be transferred (pseudonymized) to the sponsoring center.

**Table 1. Study procedures**

| Measurement                                                                                               | Pre-operative (baseline) | Surgery Day 0 | Follow-up (post-operative) |                         |                         |                         |
|-----------------------------------------------------------------------------------------------------------|--------------------------|---------------|----------------------------|-------------------------|-------------------------|-------------------------|
|                                                                                                           |                          |               | 6-18 weeks                 | 12 months (+/- 1 month) | 36 months (+/- 1 month) | 60 months (+/- 1 month) |
| CT-scan                                                                                                   | X*                       |               |                            | (X)*                    | (X)*                    | (X)*                    |
| Audiometry                                                                                                | X*                       |               | X*                         | X*                      |                         |                         |
| Visit outpatient clinic and micro-otoscopy                                                                | X*                       |               | X*                         | X*                      | X*                      | X*                      |
| Inclusion                                                                                                 | X                        |               |                            |                         |                         |                         |
| Randomization                                                                                             | X                        |               |                            |                         |                         |                         |
| Surgery                                                                                                   |                          | X*            |                            |                         |                         |                         |
| OQUA                                                                                                      | X                        |               | X                          | X                       | X                       |                         |
| EQ-5D-5L                                                                                                  | X                        |               |                            | X                       | X                       |                         |
| HUI-3                                                                                                     | X                        |               |                            | X                       | X                       |                         |
| iMCQ                                                                                                      | X                        |               |                            | X                       | X                       |                         |
| iPCQ                                                                                                      | X                        |               |                            | X                       | X                       |                         |
| DW-MRI scan                                                                                               |                          |               |                            | X*                      | X*                      | X*                      |
| Registration of recurrent or residual disease (if applicable)                                             |                          |               | X*                         | X*                      | X*                      | X*                      |
| (x) = depending on the necessity as judged by the treating physician, in line with best standard practice |                          |               |                            |                         |                         |                         |

#### **6.4 Withdrawal of individual subjects**

Subjects can leave the study at any time for any reason if they wish to do so without any consequences. The investigator can decide to withdraw a subject from the study for urgent medical reasons.

#### **6.5 Replacement of individual subjects after withdrawal**

See also section 4.4 sample size calculation. To anticipate possible withdrawal a 10% margin is taken into account to still provide sufficient power (of 0.80). An intention to treat analysis will be used, there is no reason to replace patients after withdrawal.

#### **6.6 Follow-up of subjects withdrawn from treatment**

During the study, each patient will stay in care of their own otorhinolaryngologist and audiologist. In case a patient is withdrawn from the study he/she will remain within regular medical care.

#### **6.7 Premature termination of the study**

In case of serious adverse events with higher frequency than reasonably might be expected and related to the mentioned surgical interventions, the research group will discuss further continuation of the study or possible pre-emptive termination.

#### **6.8 Patient and public involvement (PPI)**

This study will benefit from the expertise and input of patient representatives from relevant organizations in both participating countries: Hoormij (Netherlands) and Hoornetwerk (Belgium). Representatives will be consulted at predefined time points throughout the study, including during finalization of the study design, development of participant materials, and interpretation and dissemination of results. In addition, structured consultation meetings will be organized at least every six months to ensure ongoing input on study procedures and aspects relevant to patient experience. Support from both organizations has been confirmed, and letters documenting their willingness to contribute are included as an appendix to the protocol. An overview of the planned roles and timing of patient organization involvement across the different phases of the study is provided in a participationmatrix included in the appendix.

### **7. SAFETY REPORTING**

#### **7.1 Temporary halt for reasons of subject safety**

In accordance to section 10, subsection 4, of the WMO, the sponsor will suspend the study if there is sufficient ground that continuation of the study will jeopardise subject health or safety. The sponsor will notify the accredited METC without undue delay of a

temporary halt including the reason for such an action. The study will be suspended pending a further positive decision by the accredited METC. The investigator will take care that all subjects are kept informed.

## 7.2 AEs, SAEs and SUSARs

### 7.2.1 Adverse events (AEs)

Adverse events are defined as an undesirable experience occurring to a subject during the study. Adverse events that will be reported are the following: Complications during or after surgery (e.g. wound infection, post-operative bleeding, damage to the taste nerve resulting in change in taste, tinnitus). These are the same complications that are also mentioned by the treating physician in standard clinical care and for which informed consent is asked when discussing the surgical operation. From professional experience we will report complications that occur within the first 6 weeks after surgery. We consider this to be a relevant period in which complications due to the intervention can occur.

### 7.2.2 Serious adverse events (SAEs)

A serious adverse event is any untoward medical occurrence or effect that

- results in death;
- is life threatening (at the time of the event);
- requires hospitalisation or prolongation of existing inpatients' hospitalisation;
- results in persistent or significant disability or incapacity; or
- any other important medical event that did not result in any of the outcomes listed above due to medical or surgical intervention but could have been based upon appropriate judgement by the investigator.

An elective hospital admission will **not** be considered as a serious adverse event.

**This study is expected to pose a negligible risk for patients; any SAEs occurring during the study period are expected to be related to the standard treatment and not to the study intervention.** SAE's which could occur as a result of the operation and are always discussed with the patient beforehand as part of standard care are: damage to the inner ear (resulting in perceptive hearing loss or dizziness), damage to the facial nerve causing facial paralysis, intracranial complications. These will only be reported if they occur during or within the first six weeks after surgery as a later onset cannot be seen as a consequence of the intervention.

The investigator will report all SAEs to the sponsor without undue delay after obtaining knowledge of the events. The investigator reports this to the principal investigator and coordinating investigator of the sponsor (UMC Utrecht) per secured e-mail. The sponsor

will report the SAEs through the web portal *ToetsingOnline* to the accredited METC that approved the protocol, within 7 days of first knowledge for SAEs that result in death or are life threatening followed by a period of maximum of 8 days to complete the initial preliminary report. All other SAEs will be reported within a period of maximum 15 days after the sponsor has first knowledge of the serious adverse events.

### **7.3 Follow-up of adverse events**

From professional experience we will report complications that occur within the first 6 weeks after surgery. We consider this to be a relevant period in which complications due to the intervention can occur. All AEs will be followed until they have abated, or until a stable situation has been reached. Depending on the event, follow up may require additional tests or medical procedures as indicated, and/or referral to the general physician or a medical specialist. SAEs need to be reported till end of study within the Netherlands, as defined in the protocol.

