When Mercke first presented his results, the so called 'diffusion weighted magnetic resonance imaging' (DW-MRI) was not yet developed, making the detection of cholesteatoma during follow-up more difficult. At this time, patients traditionally underwent a 'second-look' operation, meaning that after a certain period the ear was surgically opened again to check if the disease had come back. Surgeons that are opposed to or do not utilize the obliteration technique may be afraid that it might be more challenging to detect and remove a cholesteatoma that might have been left behind after obliteration. "The main limitation of the technique is the inability to explore the mastoid cavity during follow-up with the risk of developing a "silent cholesteatoma", making radiological follow-up essential"(6). The development of the DW-MRI changed this somewhat by providing more diagnostic assurance and is currently used for the follow-up of patients that have been operated on. With the invention of the DW-MRI, the obliteration technique was therefore reintroduced and performed also subsequent to the CWU approach as patients could be followed more reliably and more otologists started believing in and using the obliteration technique. However, a limitation of radiological follow-up is the sensitivity of a DW-MRI, which ranges from 40-100% and the fact that cholesteatoma's are only detected when they are larger than 3mm in size (7–16).

Recently, van der Toom et al. showed in their systematic review that mastoid obliteration seems to reduce recurrence rates for both the CWD and CWU approach when compared to CWD and CWU without obliteration (17). While they found recurrent and residual disease rates of 5.9% and 5.8%, respectively, for the CWD technique, the outcomes for CWU tympanomastoidectomy were better. For the latter technique, they presented a recurrent disease rate of 0.28% and a residual disease rate of 4.2%. Combining the CWU tympanomastoidectomy and obliteration technique therefore seems a good solution to preserve the normal anatomy of the ear canal, as well as minimize the chance of contracting recurrent or residual cholesteatoma.

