### **10.5 Temporary halt and (prematurely) end of study report**

The investigator/sponsor will notify the accredited METC of the end of the study within a period of 8 weeks. The end of the study is defined as the last patient's last visit. The sponsor will notify the METC immediately of a temporary halt of the study, including the reason of such an action. In case the study is ended prematurely, the sponsor will notify the accredited METC within 15 days, including the reasons for the premature termination. Within one year after the end of the study, the investigator/sponsor will submit a final study report with the results of the study, including any publications/abstracts of the study, to the accredited METC.

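### Sections 7.2.2 and 7.3 give conflicting reporting periods for operation-related SAEs that begin after week six, and the longer period names only the Netherlands

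*Protocol*

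**What the plan says.** Section 7.2.2 names three groups of serious events that could follow the operation: damage to the inner ear, and "damage to the facial nerve causing facial paralysis, intracranial complications". It then says: "These will only be reported if they occur during or within the first six weeks after surgery". The reason given is that an event starting later cannot be attributed to the intervention.

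The next paragraph of the same section sets a duty with no time limit and no country limit: "The investigator will report all SAEs to the sponsor without undue delay after obtaining knowledge of the events".

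Section 7.3 first repeats the short window for complications: "From professional experience we will report complications that occur within the first 6 weeks after surgery". It closes with a different rule for serious events: "SAEs need to be reported till end of study within the Netherlands, as defined in the protocol". Section 10.5 supplies the end point: "The end of the study is defined as the last patient's last visit". Sections 6.1.1 and 6.3 (Table 1) plan follow-up to 60 months.

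Section 9.1 says that the Belgian centre works under its own local regulations, which may differ from the Dutch act. The protocol states no SAE period for Belgium.

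The SAE reports have two stated uses. Section 6.7 makes an unexpectedly high frequency of SAEs related to the surgery the trigger for discussing early termination. Section 10.4 includes SAEs in the yearly report to the ethics committee. Section 8.3 plans no interim analysis.

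**The concern.** An investigator who sees a listed event, such as an intracranial complication, some months after surgery cannot tell from the protocol whether to report it as an SAE. One sentence in 7.2.2 says no, the next paragraph says yes, and 7.3 says yes for a Dutch centre. Centres acting in good faith could act differently, and the SAE count would then depend partly on which sentence each centre followed.

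The reason for the short window is also open to question. Section 1 says that cholesteatoma without surgery can lead to brain abscess, meningitis, facial nerve palsy and lasting loss of hearing or vestibular function. These overlap with the three groups in 7.2.2. Section 1 also cites a review on obliteration: "The main limitation of the technique is the inability to explore the mastoid cavity during follow-up", with a risk of silent disease. Serious consequences of disease left behind would be expected late rather than in the first six weeks. A rule that treats every later onset as unrelated excludes them without looking at the case.

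At stake is whether the safety counts behind 6.7 and 10.4 are complete, and whether they mean the same thing in every centre.

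**Working it through.** No stated figure needs reproducing here. The check sets the instructions side by side for an SAE that begins after week six.

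| Instruction | Listed SAE (inner ear, facial nerve, intracranial) | Any other SAE |
|---|---|---|
| 7.2.2, six-week sentence | do not report | not covered |
| 7.2.2, investigator's duty | report | report |
| 7.3, Dutch centre | report until end of study | report until end of study |
| 7.3, Belgian centre | silent; 9.1 refers to local rules | silent; 9.1 refers to local rules |

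Three things follow.

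1. The listed events are a subset of all SAEs, so the first row contradicts the second and third rows for those events. For other SAEs there is no contradiction.
2. Up to week six, the instructions agree for the listed events. The disagreement begins only after that.
3. For Belgium, 7.2.2 still applies, with its internal conflict. What is missing is a stated end to the period.

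The length of time over which the rules disagree can be worked out:

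- Inputs: six weeks (7.2.2) and 60 months of follow-up (6.1.1 and Table 1).
- Follow-up in weeks: 60 × 365.25 / 12 / 7 = 260.9.
- Share covered by the six-week window: 6 / 260.9 = 2.3%.
- Remainder: 260.9 − 6 = 254.9 weeks, or 97.7%.

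This is a share of planned calendar time per patient. The protocol gives neither the rate nor the timing of SAEs, so it cannot be turned into a number of missed events.

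**The case against.** The best defence is that the texts can be read together: a general rule (all SAEs, to end of study) with an exception for three listed event types after week six. The closing words of the 7.3 sentence may point back to that exception. This reading is possible, so it would go too far to say that the instructions can never be followed together. But 7.3 states no exception, and neither does the all-SAEs duty in 7.2.2. The reader has to supply it. Even on this reading, late listed events go unreported and the Belgian period stays unstated.

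Several stronger conclusions are tempting, and the protocol does not support them:

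- **All SAEs stop at six weeks.** The limit covers only the listed events.
- **The main danger of obliteration goes unmeasured.** Residual disease is part of the primary endpoint. It is sought by micro-otoscopy and DW-MRI at 1, 3 and 5 years in both arms, and findings at revision surgery are collected (6.1.2). Section 1 itself says that DW-MRI has eased the worry about silent disease. What might be missed is narrower: late serious consequences of such disease, as SAEs.
- **The comparison between arms is biased.** Randomisation is stratified by centre (6.2), so different periods in different centres would not by themselves favour one arm.
- **About 98% of events are lost.** That percentage describes time, and surgical complications may well cluster early.
- **Belgian centres have no SAE duty.** The all-SAEs sentence in 7.2.2 is not limited to one country, and local rules apply.

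It is also fair to say that 6.7 has no numerical threshold and concerns only events related to the surgery. That limits the effect of a missing report. However, the six-week sentence settles relatedness in advance by date of onset, so a late event would not reach that discussion.

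**Conclusion.** The point holds as an inconsistency in safety reporting. For listed operation-related SAEs with onset after week six, 7.2.2 conflicts with itself and with 7.3, over about 255 of 261 weeks of planned follow-up. No SAE period is stated for Belgium. The likely consequence is SAE counts that are incomplete and not comparable across centres, where 6.7 and 10.4 use them.

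The statement that later onset cannot result from the intervention is not justified in the protocol and sits poorly with Section 1. This does not show that late facial nerve or inner-ear damage is caused by surgery. It shows only that the protocol's own account gives a route by which serious events could arise late.

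The conclusion assumes that the six-week sentence refers to the events listed just before it, and that 7.3 means all SAEs, as its wording suggests. The number of events affected cannot be estimated from the protocol. The primary endpoint is unaffected.

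**What to change.** Reconcile 7.2.2 and 7.3 into one explicit SAE reporting period that applies to all centres in both countries. State plainly whether the listed operation-related events follow that period or are an exception to it. If Belgian rules require something different, say so and give the period. The choice of period belongs to the sponsor and the ethics committee.

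Either justify the statement about later onset or remove it.

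The six-week window for recording complications in 6.1.2 need not change on this account, because a complication window can coexist with a different SAE period. A cross-reference would prevent the two from being confused.

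The cost is an amendment to the wording of two sections and a notice to centres. Depending on the period chosen, there may be slightly more SAE reporting at the visits already planned at 12, 36 and 60 months. No new visits or tests are needed.
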